#### Statistical methods

All clinicopathological and procedural variables will be described and analysed. Continuous variables will be summarized with standard statistics including, means, standard deviations, medians and ranges. Categorical variables will be summarized with frequencies. When appropriate, box plots and cross tables will be used for descriptive statistics of continuous and categorical variables, respectively. *P*-values below 0.05 will be considered significant. All calculations will be generated by statistical package for social sciences software (SPSS®). Calculation of the number of patients that will be needed to address our primary endpoint with a power of 80% and a 5% type I error rate is described in the sample size calculation section.

Univariate survival analysis will be performed using the Kaplan-Meier method. Differences in survival lengths will be analysed using the log rank test. To determine hazard ratios (HR) for multivariate analysis, Cox regression will be used. Significance of differences for continuous and categorical data will be analysed using the Mann-Whitney U test and Chi-square test respectively. When appropriate, box plots and cross tables will be used for descriptive statistics of continuous and categorical variables, respectively. OS will be estimated by the Kaplan-Meier method with corresponding two sided 95% Cl’s for survival proportions.

Primary and assisted technique efficacy rates (PTE, ATE) defined as the percentage of target lesions that have recurred after the initial local treatment and after additional local treatments regardless of the technique(s) used to treat the recurrence with a minimum follow-up period of 12 months after the last focal therapy;- Direct and indirect total cost of care for both treatment arms will be registered in the cost-effectiveness data collection matrix. Based on this matrix a cost–utility analysis, measured in terms of years of full health lived, using quality-adjusted life years will be prospectively calculated. Cost-effectiveness will be expressed as an ICER, the ratio of change in costs to the change in effects.

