##### Cost analysis

the primary health outcome measure in this economic evaluation will be the total quality adjusted life years (QALY) per trial arm. QALYS will be calculated by using the utility scores linked to the various health states of the EQ-5D; in essence the length of time a patient spends in a particular health condition is weighed by the corresponding utility. Missing data on costs and utilities will be imputed using multiple imputation. The difference in total costs and total QALYs in both arms will be used to calculate the incremental cost-effectiveness ratio (ICER): the cost per QALY gained (or cost-savings per QALY gained or lost), using the formula: ICER = (Cintervention - Ccontrol)/(QALYintervention - QALYcontrol). Cost and health effect will be discounted using the Dutch discount rates of 1.5% for health effects and 4% for costs. In addition, to allow comparison with international studies, discount rates of 3% for both health effects and costs will be used as well. To assess the impact of uncertainty, a probabilistic sensitivity analysis will be performed using the non-parametric bootstrap with 5000 replications. The results will be presented on cost-effectiveness planes. In addition, ICER acceptability curves will be presented and univariate sensitivity analyses will be performed focusing on uncertainty around most important costs-items.

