#### Dissemination policy

To ensure optimal implementation we used the framework of *Fleuren* et al. [35]; consisting of patient, innovation, organization and socio-political determinants. Although clinical equipoise between surgery and ablation is reached for small CRLM, the results from recent meta-analyses, such as the most recent one by Meijerink et al. [36], do not support thermal ablation for resectable CRLM outside clinical trials. Hence, patients suitable for COLLISION will have to choose between surgery (+/− ablation for unresectable CRLM) and trial participation.

With 15.549 new cases of colorectal cancer in the Netherlands (2015) approximately 4% of them will have ≥1 resectable and ablatable CRLM [1]. At this moment, these lesions are treated by resection, whilst ablation may be associated with less complications and an equal or even superior oncological outcome. In other words, in the Netherlands alone an estimated target population of 625 patients per year should be eligible for COLLISION trial participation. To further facilitate implementation the trial is formally supported by the following concerning patient federations who joined the trial advisory board: The Dutch Federation for patients with cancer (NFK), the Dutch society for patients with gastro-intestinal and hepato-, pancreatico-, biliary cancers (SPKS) and the Dutch society for image-guided treatment of cancer (SBBvK).

The study is embedded within the multidisciplinary Dutch Colorectal Cancer Group (DCCG). DCCG is a collaboration between medical disciplines that are relevant for the diagnosis and treatment of colorectal cancer (surgical oncology, radiotherapy, medical oncology, pathology, radiology, gastroenterology, genetics). Patients will be recruited throughout the country and treated in one of the qualifying and selected high-volume centres. We will ensure that the scientific community, patients and professional organizations will be constantly kept up to date on the obtained results.

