In order to qualify for reimbursement the Dutch health care institute (ZiNL) demands the best available evidence. Currently, thermal ablation is only approved for truly unresectable and small CRLM. Outside the setting of the trial ablations of resectable CRLM are off-guideline and hence not reimbursed. The direct and indirect costs of thermal ablation are considerably lower than that of surgery. We expect even lower indirect costs for patients treated within the study, primarily because thermal ablation of resectable CRLM in patients who by definition qualify as suitable for surgery may be associated with an even lower complication-rate.

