In conclusion, a recently published systematic review and meta-analysis reported that further randomized assessments of thermal ablation with curative intent to current-day palliative chemotherapy alone should be considered unethical [36]. Therefore, the highest achievable evidence level for unresectable CRLM seems to be reached. According to above mentioned superior safety profile, lower complication-rate and competitive long term survival after thermal ablation for CRLM challenges liver surgery and fiats the setup of this randomized controlled trial. If thermal ablation for resectable CRLM proves to be non-inferior to surgery, a reduction of the post-procedural morbidity and mortality, length of hospital stay and incremental costs can be expected, with better quality of life and without compromising oncological outcome.

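### The protocol lets the ICER be read as cost savings per QALY gained, which is not a valid measure if ablation is cheaper with equal or better QALYs

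*Protocol article*

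**What the plan says.** The protocol article lists the ICER and QALYs among its main secondary endpoints. Under Cost-effectiveness analysis, Cost analysis, it takes the difference between arms in total costs and in total QALYs and divides the first by the second, ablation minus resection. It describes the result as "the cost per QALY gained (or cost-savings per QALY gained or lost), using the formula". Statistical methods repeats the choice of summary: "Cost-effectiveness will be expressed as an ICER, the ratio of change in costs to the change in effects".

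For uncertainty, Cost analysis states that "a probabilistic sensitivity analysis will be performed using the non-parametric bootstrap with 5000 replications" and that "The results will be presented on cost-effectiveness planes". It adds acceptability curves and univariate sensitivity analyses on the main cost items. It gives no rule for dominance, no net-benefit measure and no instruction on how to handle a negative ratio.

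The article gives no expected cost or QALY difference, but it indicates a direction:
- On costs, Dissemination policy says: "The direct and indirect costs of thermal ablation are considerably lower than that of surgery".
- On outcome, the same section says that "ablation may be associated with less complications and an equal or even superior oncological outcome".
- The closing paragraph of the Discussion expects, if non-inferiority is shown, a result "with better quality of life and without compromising oncological outcome".

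**The concern.** The parenthesis names two ways to read the ratio when ablation saves money: per QALY gained and per QALY lost. The second describes a real trade-off, namely how much is saved for each QALY given up. The first describes no trade-off, because ablation is then better on both counts. Dividing one advantage by the other gives a number that does not measure value.

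The article's own expectations point towards this situation. If they are borne out, the figure meant to express cost-effectiveness would be a negative ratio, or a ratio with a denominator close to zero. Its prescribed reading would make a larger health benefit look like a smaller return.

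**Working it through.** **Inputs.** The ratio is ΔC/ΔQ, with ΔC and ΔQ taken as ablation minus resection (Cost analysis). The article gives no numerical ICER, cost difference, QALY difference or willingness-to-pay threshold, so there is no figure of its own to reproduce. The sizes below are assumptions for illustration: a cost difference of EUR 5,000 in either direction, QALY differences of 0.01 to 0.10, and thresholds λ of EUR 20,000, 50,000 and 80,000 per QALY. Steps 1 to 3 are algebra and hold for any size.

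**1. Fixed saving, growing QALY gain.** For a saving S > 0 and ΔQ > 0, the saving per QALY gained is S/ΔQ, which falls as ΔQ rises.
- 5,000/0.01 = 500,000
- 5,000/0.05 = 100,000
- 5,000/0.10 = 50,000

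The best of the three results shows the smallest saving per QALY gained. This concerns absolute size; the signed ICER rises from -500,000 towards zero.

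**2. Equal QALYs.** At ΔQ = 0 the ratio is undefined. With ΔC negative, it tends to minus infinity as ΔQ approaches zero from above and to plus infinity from below.

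**3. Opposite quadrants share a value.** (-a)/(+b) = (+a)/(-b).
- Dominant ablation: -5,000/+0.05 = -100,000
- Dominated ablation: +5,000/-0.05 = -100,000

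The same-sign quadrants also share a value: -5,000/-0.10 and +5,000/+0.10 both give +50,000. There the article's labels, savings per QALY lost and cost per QALY gained, tell the two cases apart and are correct.

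**4. Net monetary benefit on the same inputs.** NMB = λ·ΔQ - ΔC. At λ = 50,000, for example, the first row is 50,000 × 0.01 + 5,000 = 5,500.

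| ΔC | ΔQ | ΔC/ΔQ | NMB, λ = 20,000 | NMB, λ = 50,000 | NMB, λ = 80,000 |
|---|---|---|---|---|---|
| -5,000 | +0.01 | -500,000 | 5,200 | 5,500 | 5,800 |
| -5,000 | +0.05 | -100,000 | 6,000 | 7,500 | 9,000 |
| -5,000 | +0.10 | -50,000 | 7,000 | 10,000 | 13,000 |
| +5,000 | -0.05 | -100,000 | -6,000 | -7,500 | -9,000 |

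Net benefit rises with the QALY gain and separates the dominant case from the dominated one at every threshold shown.

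**The case against.** The strongest reply is that an ICER with bootstrap, plane and acceptability curve is a conventional design, and that the fault lies in one word of a parenthesis. Much of this stands. The plan computes both differences before dividing, and the plane plots them, so a reader who sees the plane can tell dominant from dominated. The shared value misleads only someone shown the ratio alone.

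A reader might go further and infer that the plan will produce a meaningless confidence interval for the ICER, or will rank or average ratios. It proposes none of these. A reader might also infer that the univariate sensitivity analyses are tied to the ratio, but the article names no output for them. Nor does it say that reimbursement rests on the ICER. Dissemination policy says only that the Dutch health care institute asks for the best available evidence.

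The expected direction is also partly inferred. The statement on oncological outcome is hedged, and the one on quality of life is conditional on non-inferiority. Cheaper with some QALY loss remains possible: the Discussion cites a hazard ratio of 1.92 against radiofrequency ablation alone, and the design tolerates a hazard ratio up to 1.3. In that case the article's reading per QALY lost is right.

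What does not stand is the suggestion that this is detail for a fuller analysis plan. A missing dominance rule could be left there. A stated reading that is invalid in the direction the article itself suggests is an error in the text, and the planned displays do not correct it.

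**Conclusion.** The point holds in a limited form. The article states a reading of its ICER, savings per QALY gained, that is invalid whenever ablation is cheaper and better, and the ratio has no value at equal QALYs. The algebra needs no assumptions; the monetary and QALY sizes are illustrative, and the QALY direction is inferred.

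The planes and acceptability curves limit the damage, so the risk is confined to the point ICER and how it is reported. The overall survival analysis, the sample size and the data collection are unaffected. The documents do not support the stronger conclusion that the ICER should be abandoned or that the economic evaluation as a whole is unsound. The correction is still worth making, because Statistical methods makes this ratio the expression of cost-effectiveness.

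**What to change.** - In Cost analysis, remove the gained half of the cost-savings reading and keep savings per QALY lost.
- Report the cost difference and the QALY difference separately, each with its uncertainty.
- Quote an ICER only when both differences have the same sign. When the signs differ, state that ablation is dominant or dominated. If the QALY difference is zero, report the cost difference without a ratio.
- Add incremental net monetary benefit, λ·ΔQ - ΔC, at pre-stated willingness-to-pay thresholds, from the same bootstrap replicates and alongside the ICER.
- Bring the sentence in Statistical methods into line.

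The cost is a change of wording plus one extra summary. The data and the 5000 replications stay the same. The one small downside is that the thresholds must be named in advance.

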#### Dissemination policy

To ensure optimal implementation we used the framework of *Fleuren* et al. [35]; consisting of patient, innovation, organization and socio-political determinants. Although clinical equipoise between surgery and ablation is reached for small CRLM, the results from recent meta-analyses, such as the most recent one by Meijerink et al. [36], do not support thermal ablation for resectable CRLM outside clinical trials. Hence, patients suitable for COLLISION will have to choose between surgery (+/− ablation for unresectable CRLM) and trial participation.

With 15.549 new cases of colorectal cancer in the Netherlands (2015) approximately 4% of them will have ≥1 resectable and ablatable CRLM [1]. At this moment, these lesions are treated by resection, whilst ablation may be associated with less complications and an equal or even superior oncological outcome. In other words, in the Netherlands alone an estimated target population of 625 patients per year should be eligible for COLLISION trial participation. To further facilitate implementation the trial is formally supported by the following concerning patient federations who joined the trial advisory board: The Dutch Federation for patients with cancer (NFK), the Dutch society for patients with gastro-intestinal and hepato-, pancreatico-, biliary cancers (SPKS) and the Dutch society for image-guided treatment of cancer (SBBvK).

The study is embedded within the multidisciplinary Dutch Colorectal Cancer Group (DCCG). DCCG is a collaboration between medical disciplines that are relevant for the diagnosis and treatment of colorectal cancer (surgical oncology, radiotherapy, medical oncology, pathology, radiology, gastroenterology, genetics). Patients will be recruited throughout the country and treated in one of the qualifying and selected high-volume centres. We will ensure that the scientific community, patients and professional organizations will be constantly kept up to date on the obtained results.

In order to qualify for reimbursement the Dutch health care institute (ZiNL) demands the best available evidence. Currently, thermal ablation is only approved for truly unresectable and small CRLM. Outside the setting of the trial ablations of resectable CRLM are off-guideline and hence not reimbursed. The direct and indirect costs of thermal ablation are considerably lower than that of surgery. We expect even lower indirect costs for patients treated within the study, primarily because thermal ablation of resectable CRLM in patients who by definition qualify as suitable for surgery may be associated with an even lower complication-rate.

## Discussion

The recently published primary efficacy rates (complete ablation after the first procedure) of RFA and MWA for small CRLM have approached the reported resection plane recurrence rates for similar sized lesions [6]^,^ [14–17], [21]. Hence the issue of ablation site recurrences, that has previously prevented its widespread adoption, may be outdated. The relative ease to percutaneously re-ablate potential site recurrences, nowadays in the setting of a one-day admission under conscious sedation, has further downgraded its relevance.

### Partial hepatectomy

Until relatively recent, patients with CRLM could only be cured by surgical resection of the lesions. Although no formal upper limit regarding number and size of CRLM has been established, surgical resection is nowadays considered safe and effective for patients with an adequate performance status if radical resection will leave sufficient future functioning liver parenchyma. In addition, one of the three main hepatic veins must be uncompromised and the liver remnant has to comprise a portal vein, hepatic artery and a bile duct. Clear definitions of what is regarded as resectable are lacking and vary dramatically from center to center on the basis of aggressiveness of the surgical team and the perception of the medical oncologist on when to refer patients [37]. To achieve consensus several societies for surgical oncology and hepatobiliary surgery have previously attempted to postulate resectability criteria (Table 2) [38, 39]. The objective of surgical resection for CRLM should be to remove all macroscopically visible tumour tissue with the intent to achieve cure. Histological tumour free margins and hence the confirmation of having radically resected the metastases remains essential.

Surgical resection has a 5-year OS reaching 31–58% [3, 40]. Although the number of serious adverse events of hepatic resection has decreased considerably in the past two decades, the 90-day mortality (4%) and the complication-rate (40%; major plus minor) are still high [41–43]. In 2007 data from 1059 non-cirrhotic patients who underwent major hepatectomy were analysed [43]. The total percentage of complications was 453 (43%), divided as follows: minor complications 26% (grade I 7%; grade II 19%) and major complications 17% (grade IIIa 10%, grade IIIb 2%, grade IVa 4%, grade IVb 1%). Most frequently encountered complications include per-operative major bleeding, bile duct/gallbladder injury, perforation of adjacent structures, intra-abdominal infection, wound infection, liver abscess, haematoma at incision site, pneumothorax, liver failure and death (4%) [41, 42].

### Radiofrequency ablation

Since its introduction in the late 90’s, RFA is the most studied and widely adopted ablative technique. It has emerged as a promising approach in the treatment of patients with unresectable CRLM. RFA has acquired its role in the treatment of patients with unresectable CRLM as a safe, well tolerated, easily repeatable and less invasive procedure [44, 45].

One major drawback of RFA is the heat-sink effect in highly perfused organs, such as the liver where a large tumour located near large vessels (> 3 mm diameter) is not properly treated because heat is lost to the flowing blood. Another risk of RFA is heat injury to vital structures in or surrounding the ablated area. For this reason, treatment of lesions in the proximity of other organs, large vessels and major bile ducts has to be performed with caution, and is sometimes contra-indicated [46].

The 90-day mortality of thermal ablation alone is very low (< 1%) and the complication rate is also low (6–9%) [6]. Applied to unresectable CRLM, 5-year survival rates are approaching the results reported after surgical resection, especially for patients presenting with a limited number of small-size lesions. The reported 5-year OS is 25–55% [21–29]. The recently presented long-term results from the only available randomized controlled trial shows a survival plateau of 36% after 8-years in patients with unresectable CRLM [6]. It is important to realize that these percentages are derived from studies where thermal ablation was used to treat unresectable lesions. Ruers et al. found a PFS of 16.9 months (95%CI 11.7–22.1) in a group of patients who received chemotherapy plus RFA (HR 0.63 [95%CI 0.42–0.95]). Of those 56 patients treated with RFA, 9 developed a local site recurrence (LSR) (16,1%) [6].

Complications can be divided into three different groups: related to probe placement (bleeding 0,7%, infection, tumour seeding 0–0,3%), related to energy delivery (damage to bowel, gallbladder, bile ducts 4,2%, grounding pad burns, post-ablation syndrome, hepatic vascular damage, liver failure 2,1%) and related to the general procedure (deep venous thrombosis, pulmonary embolism, referred pain, fever, nausea, vomiting, kidney failure) [47].

### Microwave ablation

MWA is known as ablative technique for tissues with a high percentage of water and has several theoretical advantages that may result in improved performance near blood vessels. Due to a much broader field of power density, MWA results in a larger zone of active heating. This increased zone allows for a more homogeneous zone of tumour cell death, both within the targeted zone and next to blood vessels. This feature is thought to make MWA less affected by heat sink. Recent developments in the field of MWA, employing higher frequency bands (2.45 GHz) or spatial energy control (thermal, field, and wavelength), claim to create more predictable, larger and more spherical ablation zones regardless of target location, tissue type or changes in tissue properties during the ablation [48].

Several studies reported a 3-,4- and 5-year OS for MWA between 35 and 79%, 35–58% and 17–18% [15, 16, 49–54]. M7ortality is ranging between 0 and 2% [15, 49, 50]. The median DFS ranges between 8 and 12 months [15, 50, 54]. Overall recurrence ranges between 39 and 72% [15, 17, 50, 51, 55, 56]. In several observational studies complications ranged between 0 and 54% [15, 16, 50, 55–57]. No studies reported the effect on quality of life after MWA.

### Partial hepatectomy versus thermal ablation

Numerous studies reported OS rates for surgery and thermal ablation techniques. Comparing RFA alone to surgery alone numerous observational studies reported corrected hazard ratios for OS between RFA and surgery alone; treatment with RFA was associated with an inferior OS (HR = 1.92; 95%CI 1.44–2.56) [22, 23, 25, 27, 58–61]. Comparing RFA plus surgery to surgery alone other studies reported corrected hazard ratios and allowed for pooling between surgery and surgery plus RFA; no significant difference in OS was found (HR = 1.29; 95% CI 0.71–2.327) [14, 18, 61, 62].

For MWA, a 3-year OS of 23% after surgery and 14% after MWA has been reported [54]. Another study showed a 4-year OS of 70% after surgery and 41% after MWA, although no formal statistical comparison with surgery alone was reported [53]. A more recently published study found 5-year OS rates for surgery versus percutaneous ablation as first intervention of 51.9 and 53%, with a median OS of 65.0 (95%CI 47.3 to 82.6) and 62.1 (95%CI 52.2 to 72.1) months, respectively [19].

Another study reported no significant difference in OS for MWA plus surgery versus surgery alone (3-year OS: 50.9% vs 48.8%) [63]. Median OS was 39 months after surgery and 28 months after MWA plus surgery. In multivariate analysis MWA was no prognostic factor for OS.

Several studies revealed that complications were significantly more common after surgery compared to RFA (relative risk [RR] = 0.47; 95%CI 0.28–0.78) [22–29, 59, 64–66]. Two studies reported serious adverse events in 21–28% after surgery vs 13–37% in the surgery + ablation group [18, 24].

Some studies compared RFA to surgery alone regarding local progression-free survival (LPFS) and DFS; RFA was inferior to surgical resection (+/− RFA) [25, 28, 58]. Comparing RFA plus surgery to surgery alone, RFA plus surgery was associated with a poor LPFS [14, 18, 24, 58, 61]. Assessing DFS, no significant difference between RFA + surgery vs surgery alone was found.

In conclusion, a recently published systematic review and meta-analysis reported that further randomized assessments of thermal ablation with curative intent to current-day palliative chemotherapy alone should be considered unethical [36]. Therefore, the highest achievable evidence level for unresectable CRLM seems to be reached. According to above mentioned superior safety profile, lower complication-rate and competitive long term survival after thermal ablation for CRLM challenges liver surgery and fiats the setup of this randomized controlled trial. If thermal ablation for resectable CRLM proves to be non-inferior to surgery, a reduction of the post-procedural morbidity and mortality, length of hospital stay and incremental costs can be expected, with better quality of life and without compromising oncological outcome.

